#### Partner notification services

The timeline and components of partner notification in the intervention arm (immediate APS) and control arm (delayed APS) are displayed in Figure 3. At sites randomized to immediate APS, health advisors encourage index participants to disclose their HIV status to sexual partners and tell them that they will be contacting their partners within the next 1–2 weeks, consistent with provider referral [17]. At sites randomized to delayed APS, health advisors encourage index participants to disclose their HIV status to sexual partners (passive referral) as per HTC guidelines; health advisors then contact partners 6 weeks after index case enrollment.

**Figure 3 Fig3:**
[figure not shown]
**Study flow for intervention versus control sites, starting from when an index participant tests HIV-seropositive.** Illustrated here are the study procedures for the intervention arm (immediate APS following index participant enrollment) and the control arm (APS delayed for 6 weeks after index participant enrollment). The star (*) indicates that the partner services involve: 1) partner tracing and enrollment; 2) HIV testing and counselling of partners; and 3) referral of HIV-seropositive partners to HIV care.

Partners are first contacted via phone. To enhance credibility and create a safe space for the ensuing conversation, health advisors introduce themselves as Ministry of Health health-care workers based at KNH, the principal National Referral Hospital in Kenya. If partners ask how their contact information was obtained, they are told that it was obtained from a NASCOP database. In the original protocol, health advisors disclosed that a sexual partner had provided the contact information, without revealing the identity of the index participant. However, partners often declined to participate unless they knew who identified them. The script was changed after the first month to facilitate enrollment while protecting the confidentiality of index participants. This was the only change made to methods after trial commencement.

Health advisors then inquire whether the partner is in a suitable environment for health information to be discussed. If so, health advisors engage in a discussion about the partner’s health status, especially recent sexual contacts, risky sexual behavior and possible exposure to HIV. For individuals who are not in a suitable environment to discuss their health status, another phone call is planned or an in-person interview is scheduled.

On the phone or in person, health advisors encourage HIV testing and describe study objectives and the consent process. Partners are invited to speak with the health advisor and test for HIV at a study site close to their location. For those who cannot come to a study site, health advisors arrange a meeting at a convenient place and time; these have included partners’ homes, workplaces, or other public areas. When health advisors meet partners, they introduce themselves again, producing staff identification badges if necessary, and obtain written informed consent for the study. HTC is then performed. Health advisors provide HIV testing to those who agree, and HIV prevention counselling to those who decline. Confidentiality is emphasized throughout the process, and the partner is assured that their information will not be shared.

If a partner cannot be reached by phone after four attempts, the health advisor travels to his/her home or work and discreetly finds a way to speak to the partner in private so that confidentiality is maintained. They then describe the study as detailed above. If a partner still cannot be found after physical tracing, the health advisor verifies the contact information with the index participant and attempts to trace again. Failed physical tracing (at least three attempts), partners with insufficient contact information, and successfully traced partners who decline study participation are documented. Due to resource constraints, partners residing >50 km from the study site are notified via phone call, and if they cannot attend a study site for enrolment, they are not enrolled but still strongly encouraged to test at the nearest HTC facility.

#### Participant follow-up

Index cases participate in three study visits: one at baseline for screening/enrolment and two follow-up visits at 6 weeks and 3 months to assess linkage to HIV care, IPV and other social harms, and risk behaviors.

Partners in the immediate APS arm participate in two visits: one at baseline for recruitment and a follow-up visit after 6 weeks to determine whether they have tested for HIV and linked to care if HIV-seropositive. Linkage to care is verified by any of the following: CCC registration number, CD4 count, WHO HIV staging, or commencement of co-trimoxazole and/or ART. Partners in the delayed APS arm have a single visit scheduled at 6 weeks after enrollment of the index, which serves as a combined recruitment and assessment for any prior notification, HIV testing, and linkage to care if HIV-seropositive.

All participants are reminded via phone call on the day prior to a scheduled visit. Any participants who miss appointments are traced by health advisors (by phone, at home, or at work) and rescheduled. Any participants who cannot be traced at the closure of each study site (after approximately 6-months duration) are considered lost to follow-up.

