### Outcome measures

Outcomes will be compared between intervention and control arms based on data collected 6 weeks after enrollment of index participants and will be analyzed at the cluster level.

Primary outcomes are as follows: 1) HIV testing of partners (number of partners of an index participant that were tested for HIV, offset by the number of partners with locator information provided by the index participant); 2) newly identified HIV-infected partners (number of partners of an index participant identified as HIV-infected, offset by the number of partners of that index participant who were HIV tested); and 3) linkage to HIV care (number of partners of an index participant who were linked to HIV care, offset by the number of partners of an index participant identified as HIV-infected; analysis will be limited to index participants with at least one HIV-infected partner).

Secondary outcomes are as follows: 1) the incremental cost per HIV-infected person identified and linked to care, including ART, and the incremental cost-effectiveness per incident HIV infection, HIV-related death, and disability adjusted life-year (DALY) averted in Kenya from payer and societal perspectives; and 2) costs of identifying >1 partner per index case.

There have been no changes to outcome measures.

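### Outcome 3 (linkage to care) is ascertained differently by arm: under the planned visits and the stated offset, a diagnosed immediate-arm partner who is then lost counts as not linked, while a missed delayed-arm partner is not counted at all

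*Protocol article*

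**What the plan says.** **Immediate arm.** Participant follow-up states: "Partners in the immediate APS arm participate in two visits". These are described as "one at baseline for recruitment and a follow-up visit after 6 weeks to determine whether they have tested for HIV and linked to care". The infection itself is diagnosed at the first contact: after consent, according to Partner notification services, "Health advisors provide HIV testing to those who agree, and HIV prevention counselling to those who decline".

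**Delayed arm.** The schedule here is different: "Partners in the delayed APS arm have a single visit scheduled at 6 weeks after enrollment of the index". The section then says of this visit: "which serves as a combined recruitment and assessment for any prior notification, HIV testing, and linkage to care if HIV-seropositive".

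**Outcome 3.** Outcome measures defines the count as the "number of partners of an index participant who were linked to HIV care". The denominator is given in these words: "offset by the number of partners of an index participant identified as HIV-infected". The one stated restriction is to index participants with at least one infected partner. Nothing requires that the partner's linkage status was ascertained.

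**Loss.** "Any participants who cannot be traced at the closure of each study site (after approximately 6-months duration) are considered lost to follow-up". Before that point, people who miss a visit are traced by phone, at home or at work and given a new appointment. Linkage may be proven by any one of several items, among them a CCC registration number, a CD4 count or the start of ART. The protocol gives no expected loss rate and does not say how a diagnosed partner with unknown linkage enters outcome 3.

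**The concern.** In the immediate arm there is an interval between the event that puts a partner into the offset (diagnosis) and the event that can put the same partner into the numerator (proof of linkage). A partner can be lost in that interval. In the delayed arm, as planned, both facts are learned at one visit, so there is no such interval.

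The same behaviour, not being reachable for a visit, is therefore scored differently. In one arm it can lower the linkage proportion. In the other it removes the partner from the calculation. Linkage is one of three primary outcomes and part of the primary objective. A null or adverse result on it could come partly from the extra visit and not from any difference in linkage.

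**Working it through.** The protocol has no figure on this point to reproduce. The sample-size section concerns partner testing only and contains no allowance for loss in outcome 3. The check follows each kind of partner through the stated definition and then puts assumed loss rates into it.

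**Step 1. Contribution to outcome 3, read literally**

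| Partner | Offset | Numerator |
|---|---|---|
| Immediate, diagnosed, linkage proven | 1 | 1 |
| Immediate, diagnosed, found not linked | 1 | 0 |
| Immediate, diagnosed, untraceable, no other proof | 1 | 0 (true status unknown) |
| Delayed, infected, single visit attended | 1 | 0 or 1 (known) |
| Delayed, single visit missed | 0 | 0 |

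The third and fifth rows are the asymmetry.

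**Step 2. Size of the effect**

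Inputs:
- *L*: share of diagnosed immediate-arm partners who are untraceable at site closure and have no other accepted proof of linkage. Not in the protocol; assumed 5% to 30%.
- *p*: true linkage. For illustration 85% in both arms, the figure the Discussion cites from the Cameroon programme. It is not an estimate for this trial.
- Loss is unrelated to linkage and, for now, occurs after diagnosis only in the immediate arm.

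Formulas:
- Observed immediate-arm linkage = p × (1 − L); observed delayed-arm linkage = p.
- Observed ratio = true ratio × (1 − L).
- Ratio if every unknown is instead taken as linked, with no true difference = [p(1 − L) + L] / p.

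| L (assumed) | Immediate arm, observed | Ratio when truth is 1.00 | True 1.20 appears as | True ratio needed to show 1.00 | Ratio if unknown = linked (truth 1.00) |
|---|---|---|---|---|---|
| 5% | 0.85 × 0.95 = 80.8% | 0.95 | 1.14 | 1/0.95 = 1.05 | 0.8575/0.85 = 1.01 |
| 10% | 0.85 × 0.90 = 76.5% | 0.90 | 1.08 | 1/0.90 = 1.11 | 0.865/0.85 = 1.02 |
| 20% | 0.85 × 0.80 = 68.0% | 0.80 | 0.96 | 1/0.80 = 1.25 | 0.88/0.85 = 1.04 |
| 30% | 0.85 × 0.70 = 59.5% | 0.70 | 0.84 | 1/0.70 = 1.43 | 0.895/0.85 = 1.05 |

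Columns 3 to 5 do not depend on the 85%; the last one does. A true ratio of 1.20 requires delayed-arm linkage of at most 1/1.20 = 83%. With 70%, for example, the immediate arm is truly 84%, is observed at 0.84 × 0.80 = 67.2% when L is 20%, and 67.2/70 = 0.96.

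**Step 3. Early-presenting delayed-arm partners**

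Study limitations reports that some delayed-arm partners came in with the index participant straight away. If they were tested then, they could also be diagnosed before linkage was checked. If a share *E* of infected delayed-arm partners is diagnosed early and lost in the same way, the factor becomes (1 − L)/(1 − E). With L = 20% and an assumed E = 5%, it is 0.80/0.95 = 0.84 instead of 0.80. It returns to 1 when E = L.

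**Step 4. Dependence on linkage among the lost**

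If lost partners truly link at rate *q*, the true immediate-arm value is p(1 − L) + qL and the observed value is p(1 − L). The factor (1 − L) is the case q = p. If q = 0, the literal count is correct for that arm. The data cannot say which holds.

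**The case against.** The strongest reply has four parts.

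1. *The handling of unknown linkage belongs in the analysis plan, which is not shown.* This stands for imputation detail, and no missing-data rule is stated. It does not dispose of the point, because Outcome measures itself fixes the numerator, the offset and the one restriction. The asymmetry follows from those and from the visit schedule.

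2. *A missed second visit is not a loss.* This stands and limits the size. Tracing continues until site closure at about 6 months, several proofs of linkage are accepted, every site has a CCC, and most sites follow up linkage by phone or home visit (Randomization). The factor applies only to partners who are untraceable and have no such proof. However, the protocol assigns the linkage determination to the visit and does not say that proof is sought elsewhere. Partners may also be tested at home or at work, so a study site's CCC may not hold their record.

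3. *Keeping every diagnosed partner in the offset is defensible and works against the trial's own hypothesis.* Partly so: it would not manufacture a benefit on this outcome. But it can hide a true one, and the delayed arm is not held to the same rule.

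4. *An offset limited to ascertained partners has its own bias.* This stands. It conditions on something that happens after randomization and is unbiased only if loss is unrelated to linkage. Untraceable partners may well be linked less often. Bounds are therefore needed alongside it.

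**Conclusion.** The concern holds as differential ascertainment of outcome 3, created by the planned visits together with the stated offset. Taken alone, and with loss unrelated to linkage, it multiplies the outcome 3 ratio by (1 − L): 0.95 at 5% loss, 0.90 at 10%, 0.80 at 20%. The direction is against assisted partner services. The actual size is unknown, because the loss rates are assumptions, and other differences between the arms may add to it or offset it.

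A reader might infer three stronger statements that the protocol does not support:
- *Only the immediate arm can lose diagnosed partners.* This fits the planned schedule, but the delayed-arm partners who presented early are an exception, and their number is not given.
- *The plan has a rule that loss equals non-linkage.* No such rule is written. It is the literal consequence of the offset.
- *Cost per person identified and linked is biased against assisted partner services.* This is not shown. That measure uses counts, a missed delayed-arm partner is also absent from them, and loss therefore lowers the counts in both arms with no known net direction.

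**What to change.** Before outcome 3 is analysed:
- Define the offset, in both arms, as HIV-infected partners whose linkage status was ascertained.
- Count as ascertained any partner for whom a proof already listed in Participant follow-up is available, such as a CCC registration number, even when the visit was missed.
- Handle diagnosed partners with unknown linkage by multiple imputation or by weighting on their baseline data, with the same rule in both arms so that early-presenting delayed-arm partners are covered.
- Report two bounds: *unknown = not linked*, which is the present definition read literally, and *unknown = linked*.
- Report the number and share of diagnosed partners with unknown linkage by arm.

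The cost is a change to one outcome definition and one analysis paragraph, with no new visits. The downside is an untestable assumption about the lost partners; the bounds show how much the result depends on it. If unknown linkage proves rare in both arms, the bounds will nearly coincide and the choice will hardly matter.

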## Discussion

Provision of partner services in the US and Europe has been shown to be safe and effective, as well as cost-effective for HIV case-finding and linkage to care [7,8]. Prior to launching similar programs in sub-Saharan Africa, it is important to evaluate HIV APS in rural and urban African settings, which have different HIV prevalences, affected populations, sociocultural milieus, and health system structures and resources. This study is the first cluster-randomized trial to evaluate HIV APS in sub-Saharan Africa and builds upon prior work in Cameroon and Malawi.

In Cameroon, evaluation of an HIV APS program (*n* = 1,462 indexes) showed that it was feasible to notify partners (60% of named partners), identify new HIV cases (50% of partners who tested), and link them to care (85% of those testing positive) [10]. However, APS in Cameroon was undertaken as a public health program within a large, faith-based organization providing medical care rather than a research study. Evaluation of the program was uncontrolled, did not document the proportion of persons who accepted the intervention, and did not include systematic long-term participant follow-up to evaluate clinical outcomes or adverse events. Thus, while the Cameroonian experience demonstrates that APS is scalable in at least one setting in sub-Saharan Africa and suggests that the intervention is effective, it does not provide the sort of evidence produced by a randomized trial. A well-designed individual-level randomized controlled trial in Malawian STI clinics [11] showed that APS was acceptable to index cases (89% of those eligible enrolled) and doubled HIV testing among partners (51% in APS versus 24% in patient referral arm). Sixty-four percent of those tested were HIV-seropositive, demonstrating that APS enriches for HIV case-finding, but the applicability of these results to lower-risk and rural populations is unclear. Our study addresses these gaps, and a randomized design ensures rigorous comparison between intervention and control arms.

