### Study limitations

There may be limitations to this study in terms of representativeness. We selected study sites to reflect the geographic, socioeconomic, and cultural diversity in Kenya. However, practical factors such as space constraints or testing volumes excluded certain facilities.

At the index participant level, certain groups may be underrepresented, as those reluctant to participate may decline referral to health advisors. For example, individuals facing stigma related to their partners—e.g., men having sex with men, commercial sex workers—may be less likely to participate for fear of discrimination. We attempted to mitigate this via staff sensitivity training and by including a site that primarily serves sex workers; however, a different study design would be required to fully address this question in key affected populations. Individuals hospitalized with advanced HIV disease and diagnosed through PITC may be excluded due to inability to consent, even though their partners are highly likely to benefit from APS.

At the partner participant level, some partners who were meant to be followed up after 6 weeks were instead brought in by the index partner immediately for notification, making it difficult to maintain site integrity. Moreover, it is difficult to trace partners who are homeless, lack reliable phone access or contact information, or reside in inaccessible regions. We excluded partners >50 km away from the study site due to resource constraints, though a nationwide program could overcome this through a health advisor network. The other issues will require solutions that balance cost-effectiveness with equity for vulnerable populations.

Some aspects of our study may be difficult to translate to a program level. The use of smartphones for data input and transmission to a central database has increased efficiency and portability and likely avoided transcription errors. However, these devices are relatively expensive and in the absence of widespread electronic medical records in Kenya, it is unclear how feasible and cost-effective this would be for scale-up of HIV APS. They may be more cost-effective in the long run compared to computers that require a power source and security measures. Finally, while blinding was not feasible with this study design, and most outcomes are objective, lack of blinding could contribute to biases, such as how intensely health advisors pursue tracing or encourage HIV testing.

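### Control-arm partner testing is recorded only for partners who are traced and enrolled, yet all partners with locator data stay in the denominator, so the rate ratio for primary outcome 1 is likely to be inflated

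*Protocol article*

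**What the plan says.** All references are to the protocol article.

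- **Control arm (Participant follow-up).** Partners have a single visit 6 weeks after the index participant enrols, "which serves as a combined recruitment and assessment for any prior notification, HIV testing, and linkage to care if HIV-seropositive".
- **Intervention arm (Participant follow-up; Partner notification services).** Partners have two visits, "one at baseline for recruitment and a follow-up visit after 6 weeks to determine whether they have tested for HIV". At the enrolment contact, once consent is given, "HTC is then performed".
- **Partners who are not enrolled (Partner notification services).** Failed traces, partners with insufficient contact details and "successfully traced partners who decline study participation are documented". Partners more than 50 km away who cannot come to a site are phoned and urged to test locally, but are not enrolled. No way of learning whether any of these partners tested is described.
- **Index participants (Participant follow-up).** They have "two follow-up visits at 6 weeks and 3 months to assess linkage to HIV care, IPV and other social harms, and risk behaviors". Partner testing is not on that list.
- **Denominator (Outcome measures).** The count of partners tested is "offset by the number of partners with locator information provided by the index participant".
- **Study limitations.** Tracing difficulty, the 50 km rule and unblinded tracing effort are acknowledged, and the section says that "most outcomes are objective". An under-count of control testing is not mentioned. Verification is described for linkage to care but not for earlier testing.

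**The concern.** The two arms create and record the counted event differently. In the intervention arm, reaching a partner usually produces the test and its record together. In the control arm, the test has to happen first, without staff, and the trial learns of it only if staff later find the partner, who must then agree to take part and report it. A control partner who tested as passive referral intends, but was never enrolled, stays in the denominator and counts as untested.

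This bears on the hypothesis for which the trial was sized, a twofold increase in partners tested. An overstated ratio would also enter the cost-effectiveness work, which uses the study's outcomes.

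**Working it through.** **The plan's own figure.** Sample size and power analysis gives a control rate λ0 = 0.1 tested partners per index participant, r = 2 (so λ1 = 0.2), k = 0.25, 60 index participants per site, two-sided α = 0.05 and 80% power. The Hayes and Moulton formula for rates is

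c = a + (1.96 + 0.84)² × [(λ0 + λ1)/60 + k²(λ0² + λ1²)] / (λ1 − λ0)²

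The fraction is (0.005 + 0.003125)/0.01 = 0.8125, and 7.85 × 0.8125 = 6.38. With a = 1 this gives 7.38, or 8 sites per arm. With a = 2 it gives 8.38, or 9 sites, as stated. The article says only that the formula was adapted, so a = 2 is an assumption. The sample size is not the problem here.

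**Model for what gets recorded.**
- q: share of partners with locator data who are reached and enrolled. It is not given. I assume 0.6 to 0.8. The only nearby figure is the 60% of named partners notified in the Cameroon programme (Discussion), and notified is not the same as enrolled.
- s: testing rate under passive referral.
- t: testing rate among reached intervention partners.
- f: self-testing in unreached partners relative to s, from 0 to 1.
- The analysis is taken as a rate ratio (log link assumed), with similar numbers of located partners per index participant in both arms.

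With equal q in both arms:
- Recorded ratio = qt / (qs) = t/s
- True ratio = [qt + (1 − q)fs] / [qs + (1 − q)fs]

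**True ratio of 2.0 (0.20 v 0.10), f = 1.** Each arm loses (1 − q) × 0.10.

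| q | Control recorded | Intervention recorded | Recorded ratio |
|---|---|---|---|
| 0.6 | 0.10 − 0.04 = 0.06 | 0.20 − 0.04 = 0.16 | 2.67 |
| 0.8 | 0.10 − 0.02 = 0.08 | 0.20 − 0.02 = 0.18 | 2.25 |

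At q = 0.6 control loses 40% of its events and intervention 20%. Control expects 0.1 × 540 = 54 events, of which 0.4 × 54, about 22, go unrecorded.

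**Observed ratio of 2.0, equal reach.**

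| q | True ratio, f = 1 | f = 0.5 | f = 0 |
|---|---|---|---|
| 0.6 | 1.60 | 1.75 | 2.0 |
| 0.8 | 1.80 | 1.89 | 2.0 |

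**No effect.** If t = s, the recorded ratio is qs/(qs) = 1.0. Equal reach creates no false effect.

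**Unequal reach (true ratio 2.0, f = 1).** With reach of 0.6 in intervention and 0.5 in control, the recorded ratio is 0.16/0.05 = 3.2. With 0.8 and 0.9 it is 0.18/0.09 = 2.0, and the inflation is gone.

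**The case against.** The strongest reply is that unreached intervention partners are missed as well. Index participants in both arms are encouraged to disclose, and intervention partners are assessed only through their own visits. This stands. It is why a reader who divides the true ratio by control reach, 2.0/0.8 = 2.5 to 2.0/0.6 = 3.3, goes too far: that treats intervention testing as fully recorded. For the same reason, the inference that a useless intervention would show 1/0.8 = 1.25 to 1/0.6 = 1.67 does not follow under equal reach. On the difference scale, with equal reach and f = 1, the loss cancels (0.16 − 0.06 = 0.10).

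A reader might also infer that the bias must always favour APS. The document does not support that. Tests prompted by the phone call to intervention partners beyond 50 km are lost, which works against APS. Missed control visits are rescheduled until site closure at about 6 months, so tests after week 6 could be credited to control. Sufficiently higher control reach would also offset the bias.

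Nor does the locator denominator carry over to diagnoses and linkage. Those outcomes are offset by partners tested and by partners identified as infected.

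Finally, the article is condensed. Index questionnaires are not shown, and the baseline one already asks what the index participant knows of each partner's HIV status, so the full protocol may hold a second source. That limits certainty. It does not remove the problem in the procedure as published, which sets out the control visit, the content of the index visits and the denominator.

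**Conclusion.** The point holds for primary outcome 1 on the planned ratio scale. Inflation is expected when three conditions meet: reach is below 100%, some unreached partners test on their own, and APS raises testing among those reached. If unreached partners never self-test, there is none.

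For equal reach of 0.6 to 0.8 and unreached partners testing at the passive rate, a true 2.0 would be reported as 2.67 to 2.25, and a reported 2.0 would reflect a true 1.6 to 1.8. Both inputs are assumptions, so this shows what is plausible and does not estimate the trial's bias. The mechanism threatens the size of a real effect more than it threatens to create one.

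**What to change.** 1. In both arms, ask the index participant at the existing 6-week visit whether and when each named partner tested.
2. Count a test from any source, but only if it is dated within the 6 weeks after index enrolment.
3. Report the enrolled fraction of located partners by arm, and the results by source.
4. Keep control partners whom the index participant brought in early in the control arm.
5. Add a sensitivity analysis that gives unassessed partners in both arms the passive testing rate seen in assessed control partners, varied from zero up to that rate.

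The cost is a few questions per partner on an existing smartphone form at a scheduled visit. The sensitivity analysis needs no new data, which matters because all 18 sites were already active at submission and new questions can cover only visits still to come. The downside is that index participants know their partners' testing imperfectly, hence the reporting by source. Looking up partners in testing registers should be limited to cases where consent and ethics approval allow it; it is not needed for the main fix.
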